### Interim analyses {21b}

No interim analyses are planned.

### Methods for additional analyses (e.g., subgroup analyses) {20b}

Subgroup analyses will be conducted to explore the differences in outcomes for those who do and do not attend telehealth sessions regularly. Additional subgroup analyses may be explored based on emergent research questions of interest.

### Methods in analysis to handle protocol non-adherence and any statistical methods to handle missing data {20c}

Analyses will be conducted on an intent-to-treat (ITT) basis [83]. Regardless of participants’ adherence to the intervention or whether they withdrew from the study, data for every participant who was randomized to either the control or intervention group will be included in ITT analyses. Analyses that include only participants who completed the intervention will also be conducted for comparison purposes. Missing data will be handled using maximum likelihood [84], which estimates values based on all available data and thus produces unbiased model parameters [85].

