**Methods:**

A two-arm randomized controlled trial (RCT) with repeated measures will be used to evaluate the efficacy of the BEAM intervention compared to TAU among a sample of 140 mothers with children aged 18 to 36 months, who self-report moderate-to-severe symptoms of depression and/or anxiety. Individuals will be recruited online, and those randomized to the treatment group will participate in 10 weeks of psychoeducation modules, an online social support forum, and weekly group teletherapy sessions. Assessments will occur at 18–36 months postpartum (pre-test, T1), immediately after the last week of the BEAM intervention (post-test, T2), and at 3 months after the intervention (follow-up, T3).

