### Eligibility criteria {10}

#### Inclusion and exclusion criteria

Eligibility includes identifying as a mother or female primary caregiver with a child aged 18–36 months; English speaking; above the age of 18; residing in Manitoba or Alberta, Canada; self-reported moderate-to-severe symptoms of depression and/or anxiety (above a clinical threshold) at the pre-test assessment that will occur prior to randomization; and consent to wearing a Fitbit. Eligible mothers will also need to be available to attend weekly telehealth sessions, complete the baseline Zoom assessment and/or Zoom orientation and complete the pre-test self-report assessment. Participants will also need access to an iOS or Android device. If a participant reports not having access to a device, they will be provided one to use for the duration of the study period. Eligible participants who consent to be randomized will be invited to participate in the study through email. In terms of exclusion criteria, mothers who report a history of attempted suicide in the past year or self-harm in the past 6 months will not be eligible for the current study as the BEAM program is not suitable to treat acute mental health needs. Instead, these participants will receive a list of mental health resources in their province that may be more appropriate.

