### Interventions

#### Explanation for the choice of comparators {6b}

The treatment as usual (TAU) control arm of the study is designed to account for the potential effects of time on depression symptoms [46]. The TAU group will continue to receive their standard care. The control group will be used to assess whether receiving the BEAM intervention is associated with improved outcomes (e.g., mental health, reduced parenting stress) compared to TAU.

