#### Criteria for discontinuing or modifying allocated interventions {11b}

Should participants disclose suicidal behavior, the clinical team will consult about these instances and advise on whether or not continued participation in the BEAM program is in the best interest of the participant. In accordance with Best Practice Guidelines for Telepsychology Services, clinical coaches may also decide to terminate a participant’s involvement in the e-health program if they deem it inappropriate for the participant to continue (e.g., if the participant cannot ensure confidentiality is maintained through access to a secure space and stable internet connection) [52]. Furthermore, participants may have discontinued access to the forum and may be denied access to the telehealth sessions if they engage in repeated violations of the terms of use (Appendix 2). In these cases, participants would still have access to psychoeducation materials and would still be invited to complete the assessments. The clinical coaches may also provide a referral to another provider or clinic if deemed appropriate.

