#### Sample size {14}

Based on the findings from a meta-analysis, digital interventions for depression that include a human therapeutic guidance component (as is the case with the BEAM program group therapy sessions) have a moderate effect on depression (*g* = .63) [78]. Thus, an a priori, one-tailed, two-group power analysis was conducted using a moderate effect size (*d* = .5) using the G* Power 3 software [79]. The power analysis indicated that we would need 51 participants per group to reach 80% power (*α* = .05) to detect a clinically significant change in depression. To account for anticipated attrition of approximately 25%, a total sample of 140 with 70 in each group (intervention and control) will be the target for recruitment.

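### The completer-only and regular-attender analyses select on behaviour that arises after randomisation and only in the BEAM arm, so neither can show the effect of receiving the programme

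*Protocol article*

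**What the plan says.** Section {20c} of the protocol article sets the main analysis: "Analyses will be conducted on an intent-to-treat (ITT) basis". Every randomised participant is kept, whatever her adherence. The same section then adds: "Analyses that include only participants who completed the intervention will also be conducted for comparison purposes". Section {20b} adds a second analysis under the subgroup heading: "Subgroup analyses will be conducted to explore the differences in outcomes for those who do and do not attend telehealth sessions regularly".

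The programme is given to one arm only. According to the abstract, "those randomized to the treatment group will participate in 10 weeks of psychoeducation modules, an online social support forum, and weekly group teletherapy sessions". For the control arm, section {6b} says: "The TAU group will continue to receive their standard care".

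Availability for sessions is checked in everyone before randomisation (section {10}: "Eligible mothers will also need to be available to attend weekly telehealth sessions"). Actual attendance and completion are not baseline variables. Section {11b} also lets the team end a participant's involvement after randomisation, and under that section "participants may have discontinued access to the forum and may be denied access to the telehealth sessions".

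**The concern.** A TAU mother has no programme to complete and no session to attend. Read literally, the completer analysis leaves TAU out. Otherwise it sets a self-selected part of the BEAM arm against the whole TAU arm. The attendance analysis is labelled a subgroup analysis, but its groups are formed by conduct during the trial and not by a characteristic fixed at baseline.

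If completing or attending is related to how a mother would have fared anyway, both analyses mix programme effect with prognosis. Section {11b} supplies one such link from within the protocol: some BEAM mothers may leave the programme because of their state or conduct, while comparable TAU mothers stay in the comparison. At stake is how these supportive results are read when they appear beside the ITT estimate.

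**Working it through.** **Inputs from the protocol.** Section {14}: 70 per arm, planned d = 0.5, 51 per group for 80% power at alpha 0.05, about 25% attrition. The calculation is described thus: "one-tailed, two-group power analysis was conducted".

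**The plan's own figure.** A one-sided two-sample t test with d = 0.5 needs 51 per group (power 0.806). Inflating gives 51/0.75 = 68 per group, or 136 in total, against 140 stated. These figures serve the ITT comparison and are not disputed. d = 0.5 is used below only as a yardstick.

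**Assumed inputs, not in the protocol.** p is the share of the BEAM arm that completes. Delta is the difference in SD, without BEAM, between would-be completers and the other mothers; positive means completers fare better.

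**Bias of completers against all TAU.** Suppose BEAM has no effect. Randomisation makes the whole BEAM arm comparable with TAU, so the TAU mean equals p x (completer mean) + (1-p) x (non-completer mean). Subtracting this from the completer mean leaves

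bias = (1-p) x delta.

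| p | delta | bias (SD) | share of d = 0.5 |
|---|---|---|---|
| any | 0 | 0 | 0% |
| 0.7 | 0.3 | 0.3 x 0.3 = 0.09 | 18% |
| 0.7 | 0.5 | 0.3 x 0.5 = 0.15 | 30% |
| 0.5 | 0.3 | 0.5 x 0.3 = 0.15 | 30% |
| 0.5 | 0.5 | 0.5 x 0.5 = 0.25 | 50% |

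A negative delta gives the same sizes against BEAM.

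**Bias of the attendance contrast.** Let p now be the share attending regularly. Attenders against non-attenders is off by all of delta. Showing each group against TAU does not help: attenders are off by (1-p) x delta and non-attenders by -p x delta. With p = 0.7 and delta = 0.3 that is +0.09 and -0.21, a gap of 0.30.

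**Check by simulation.** 20,000 trials per scenario, 70 per arm, true effect zero, and an assumed correlation rho between the propensity to complete and good prognosis. The completer columns give one-sided / two-sided rejection at 5%, because the power calculation is one-tailed and section {20a} does not state sidedness. The attender test is two-sided.

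| share completing | rho | completers vs TAU | attenders vs non-attenders |
|---|---|---|---|
| 75% | 0 | 5% / 5% | 5% |
| 75% | 0.2 | 12% / 8% | 23% |
| 75% | 0.3 | 17% / 11% | 45% |
| 50% | 0.2 | 19% / 12% | 27% |
| 50% | 0.3 | 32% / 21% | 52% |

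The two approaches agree. In this model a 75% share with rho = 0.3 implies delta = 0.508, and 0.25 x 0.508 = 0.127, which matches the simulated 0.128.

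**The case against.** ITT is the stated basis. The completer analysis is offered only as a comparison and the attendance analysis only as exploration. A reader might infer that the protocol presents them as the effect of the programme when used. It does not say so anywhere, and the primary conclusion does not depend on them. This stands, and it limits the point to supportive results.

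A reader might also infer that these results will come out larger than ITT. The protocol does not establish that. The outcome is change from baseline in a repeated-measures model, so a baseline difference need not carry over in full. More severe mothers may drop out and leave completers with less room to improve, mothers in greater need may attend more, and those who recover may stop. The sign and size of delta are unknown. This also stands.

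Further, the comparator for completers and the definitions of completion and regular attendance may be given in an analysis plan that is not shown. Their absence is not counted here. Definitions would not cure the problem, because any threshold on completion or attendance is reached after randomisation and in BEAM only.

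Finally, an instrumental analysis has its own weaknesses. With the number of sessions as exposure it would credit sessions with whatever the videos, mood tracking and forum achieve, and section {11b} leaves the psychoeducation material open to mothers who are denied sessions. With any use as exposure it may barely differ from ITT. Both points are right and shape the fix.

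**Conclusion.** The point holds for these two supportive analyses. Both depend on conduct after randomisation that is possible in one arm only, so neither is a randomised comparison and neither answers what receiving BEAM does. That follows from the protocol's text and needs no assumption.

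The size does rest on assumptions. The completer bias is (1-p) x delta: nil at delta = 0, 0.09 to 0.25 SD over the positive values tabulated (18 to 50% of the planned d = 0.5), and reversed if delta is negative. The attendance contrast carries all of delta. Adjusting for baseline PHQ-9 could remove part of either bias, but not the part due to motivation or to events during the trial.

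The sample size, the ITT analysis and the primary conclusion are untouched.

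**What to change.** - In {20c}, replace the completer-only analysis, for the received-treatment question, with a supportive complier-average causal effect. Use randomisation as the instrument and adjust for baseline PHQ-9 and the telehealth timeslot used for stratification.
- Take as exposure any programme use, by app or session, and fix this definition before outcomes are seen. Any use is preferable to a completion threshold because partial users may also benefit.
- State the exclusion restriction: allocation to BEAM has no effect on mothers who never use it.
- State that the estimate may lie close to ITT. In its simplest form it is the ITT effect divided by the share exposed, so if 90% use the programme (an assumption) it is 1/0.9 = 1.11 times ITT.
- Do not use the number of sessions as the sole exposure in an instrumental model.
- In {20b}, report completer and attendance results within BEAM as non-randomised description, without an efficacy test or efficacy wording.

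The cost is a change of wording and one standard model. Section {12} already provides for tracking logins, time in the app, forum posts and session attendance. The downside is wider intervals and one extra assumption to defend. No visit, sample size or clinical procedure changes.

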### Plans to give access to the full protocol, participant-level data, and statistical code {31c}

The full trial protocol will be made publicly available through BMC Trials. [name] and [name] will remain the custodians of the data, as the primary investigators. Data will be analyzed independently and will not be released to any third party (including the funder) before the trial is completed. In accordance with the International Committee of Medical Journal Editor’s guidelines, the authors will share de-identified patient data that underlies results presented in reports no later than 6 months after publication. The primary investigators will ensure data is available upon request.

#### Composition of the data monitoring committee, its role, and reporting structure {21a}

Study investigators will monitor the trial. There will be weekly meetings with research assistants and the primary investigators (i.e., [name] and [name]) to discuss and review each phase of the trial (e.g., recruitment, randomization, and data collection). There will also be weekly meetings with the clinical coaches and tech facilitators (i.e., those who are interacting with research participants) and primary investigators to discuss and resolve all potential questions and concerns of participants. Given the minimal risks of the program, short duration (10 weeks of intervention), and relatively small sample size, the current trial does not require a formal data monitoring committee.

#### Adverse event reporting and harms {22}

No known risks to mothers are associated with digital psychoeducational interventions. Should participants report significant distress or request additional support, clinical coaches follow up with these participants and consult with clinical supervisors using a risk management protocol. The primary investigators will check in with clinical coaches and parent coaches regularly to ensure that the study participants’ questions and concerns are responded to appropriately. No adverse events were reported in our pilot study.

We will follow the University of Manitoba’s standard procedures for reporting adverse events and protocol violations/deviations to the Research Ethics Office at the Fort Garry Campus and privacy breaches to the Access and Privacy Office.

#### Frequency and plans for auditing trial conduct {23}

The Research Ethics Board may request an audit. However, the study team has no plans for independent auditing of trial conduct.

#### Plans for communicating important protocol amendments to relevant parties (e.g., trial participants, ethical committees) {25}

Any amendments to the protocol will be submitted to the Ethics Board at the University of Manitoba, who will review and approve the amendments. If the amendment requires that revised information be communicated with enrolled research participants, this will be done through a consent addendum, which will be provided to participants through email.

#### Dissemination plans {31a}

Research findings will be disseminated to academic and nonacademic audiences, regardless of the magnitude or direction of the effect, within 12 months of trial completion. We will prepare several articles describing the effects of the BEAM program on parenting stress, mental health, and child well-being for publication in peer-reviewed journals. Papers will also be posted rapidly on preprint servers and will be open access to allow for wider reach. The principal investigators and trainees on the research team will present findings at national (e.g., Canadian National Perinatal Research meeting) and international (e.g., Society for Research in Child Development) conferences. Dissemination of infographics and bimonthly reports will occur through our partnerships with community agencies and existing knowledge users in government (e.g., [name], director of policy development, research, and evaluation, Healthy Child Manitoba). Research findings will be shared in lay summaries on lab and study websites and social media pages. We will work with media relations at the University of Calgary and our networks to disseminate research findings rapidly through local and national media. Furthermore, if trial findings substantiate the efficacy of the BEAM program we will explore opportunities for health system integration through scale-up funding.

## Discussion

Digital mental health and parenting interventions have the potential to (1) address the alarming rates of maternal mental health concerns during the COVID-19 pandemic, (2) help to protect against the adverse intergenerational consequences on child development, and (3) provide easily accessible programming to mothers who are in need of mental health and parenting supports, both during the COVID-19 pandemic and beyond. The BEAM program is a newly developed evidence-based app program that prioritizes social connection and provides psychoeducation and weekly telehealth sessions with mental health professionals. This RCT will build on a pilot trial of the intervention and provide further efficacy testing of this treatment for mothers experiencing depression and/or anxiety. Investing in maternal mental health early is expected to yield high health and economic benefits by preventing the long-term consequences of maternal depression from becoming imbedded in children’s biological and behavioral development [25]. Findings from this RCT will improve our understanding of mental health and parenting among mothers with young children and in turn help to improve maternal and child health and family well-being.

## Trial status

Recruitment began in mid-November 2021 and finished in February 2022. The date of first enrollment was November 17. The intervention was launched at the end of February 2022 (with estimated completion in October 2022 for the collection of all primary outcomes).

## Data Availability

Data will be maintained in a secure database that only the study investigators will have access to.

## Appendix 2

## Abbreviations

AUDIT: Alcohol Use Disorder Identification Test
BEAM: Building Emotion Awareness and Mental Health
BFI-10: Big Five Inventory-10
CAD: Canadian dollars
COVID-19: Coronavirus disease 2019
CSI-4: 4-item Couple Satisfaction Index
DSI-SS: Depression Symptom Index Suicidality Subscale
ECBQ: Early Child Behavior Questionnaire
CUDIT-R: Cannabis Use Disorder Identification Test - Revised
GAD-7: Generalized Anxiety Disorder – 7 item
ICMJE: International Committee of Medical Journal Editors
ITT: Intent-to-treat
MAUQ: mHealth App Usability Questionnaire
ORBIT: Obesity-Related Behavioral Intervention Trials
PACER: Parental Assistance with Child Emotion Regulation
PARYC: Parenting Young Children Measure
PHIA: Personal Health Information Act
PHQ-9: Patient Health Questionnaire
PIs: Principal investigators
PPSC: Preschool Pediatric Symptom Checklist
PROMIS: Patient-Reported Outcomes Measurement Information System
PSI: Parenting Stress Index
RCT: Randomized controlled trial
REDCap: Research Electronic Data Capture
SCS-SF: Self-Compassion Scale Short Form
SISE: Single Item Self-Esteem Scale
SPIRIT: Standard Protocol Items: Recommendations for Interventional Trials
SSEQ: Social Support Effectiveness Questionnaire
TAU: Treatment as usual
